#### Measures

We have kept the set of research measures at a minimal level, without losing meaningfulness and thoroughness. All included measures are widely used within the psychiatric clinical and research field, showing acceptable validity and reliability and good overall psychometric properties (see Table 1 for an overview of measures).

#### Primary outcome

Beck’s *Scale for Suicide Ideation* - *Current (BSSI-C)* is an interview scale with 19 items that measures a patient’s suicidal ideation at its worst point during the past 2 weeks [27]. Items are scored on a Likert scale ranging from 0 to 2, where high scores indicate severe suicidal ideation. This scale has been found to be a valid and reliable measure of suicidal ideation for use with psychiatric patients, including test-retest reliability and internal consistency scores above .90 [27]. BSSI-C will be the primary inclusion measure (see above) and will be administered at baseline (T1) and at 6 and 12 months (T3, T4).

#### Secondary outcomes

The * Suicide Attempt Self-Injury Count (SASIC)* is a brief interview covering past self-inflicted injuries, categorizing them into suicide attempts and non-suicidal acts [28]. The tool also creates counts of self-inflicted injuries by method, medical risk severity, and lethality. It has a Lifetime form and a Recent form which covers the last 6 months. The Lifetime version will be provided at baseline and the Recent form will be administered at T3 and T4.

The *Outcome Questionnaire - 45 (OQ-45)* is a 45-item questionnaire designed to measure key areas of mental health functioning (symptoms, interpersonal problems, and social role functioning). It is a widely accepted tool for identifying, tracking, and measuring behavioral health treatment outcomes and will be the measure of symptom distress in this study. OQ-45 possesses good psychometric properties when used with adult psychiatric patients, and it was recently shown to have high reliability and concurrent validity in a Norwegian sample [29]. OQ-45 will be administered at baseline and after 6 and 12 months.

*Norwegian Patient Registry (NPR)* measures are taken from administrative data on patients*.* All patients admitted to a hospital in Norway are registered in NPR. Primary NPR measures will be suicide attempts, new hospital admissions to any health treatment, and discharge diagnoses entered for the readmissions. Secondary measures will be intoxication and death by any cause.

#### Potential moderators and descriptive measures

The *Mini International Neuropsychiatric Interview (MINI)* will be used at baseline to identify DSM-VI and ICD-10 disorders associated with mood and psychosis along with other disorders. Studies have shown a good reliability and validity compared with the CIDI and the SCID-I interview [30]. In addition, the Structured Clinical Interview for DSM-IV Axis II Borderline Personality Disorder (SCID-II) will be administered to identify patients with borderline personality disorder given the importance of this group in the suicidality literature [31].

The *Generalized Self-Efficacy Scale (GSE)* is a reliable and valid measure comprising 10 items assessing the strength of an individual’s belief in the ability to respond to novel or difficult situations and to deal with a large variety of stressors [32, 33]. The GSE will be administered at baseline and after 6 and 12 months.

The *Working Alliance Inventory - ShortRevised (WAI-SR)* is a 12-item measure that will be used to assess the patient’s and therapist’s alliance after their third session together [34]. We will use the patient version of the instrument, which has high internal consistency and correlates well with other alliance measures.

Substance abuse is assessed with the *Alcohol Use Disorders Identification Test (AUDIT)* [35] and the *Drug Use Disorders Identification Test (DUDIT)* [36]. The AUDIT includes 10 questions about patterns of alcohol use and dependence. The DUDIT includes 11 questions about use or abuse of a list of drugs. Both instruments have satisfactory psychometric properties in clinical and non-clinical samples, with overall reliability above .80 and convergent validity, sensitivity, and specificity above 85 % [37, 38]. AUDIT and DUDIT will be scored at baseline.

The *Suicide Status Forms (SSFs)* are administered (initial, tracking, and outcome versions) as part of the course of care in CAMS (used for CAMS condition only). The SSF has six core rating assessments derived from theoretical approaches of Shneidman, Beck, and Baumeister and has well-established reliability and validity [39, 40].

As two of the measures (SSI-C and SASIC) did not have a Norwegian version, they were translated according to conventional procedures.

### Interventions

#### CAMS intervention

All patients randomized to the CAMS arm of the trial meet an adherence approved CAMS therapist. In brief terms, CAMS is a supportive psychotherapeutic approach that targets suicidality as the primary focus of assessment and treatment. CAMS treatment follows a predefined structure, where the SSF multipurpose assessment tool is routinely employed. A typical treatment course is characterized by employing weekly sessions of 50–60 minutes duration. Every session is initiated by filling out the SSF in a side-by-side manner. The SSF assesses and tracks the treatment process and highlights central suicide markers: psychological pain, stress, agitation, hopelessness, and self-hate (see the subsection “The CAMS approach”). In the first session, approximately 20 minutes are used to fill out the first part of the SSF as part of a “core assessment.” During the interim sessions, approximately 5 minutes are used to fill out this part of the SSF. A problem-specific treatment plan addressing the patient’s suicidal drives is jointly developed during the first session and routinely evaluated in the last part of each CAMS session. Furthermore, as part of CAMS care, a stabilization plan is developed during the first CAMS session and evaluated and improved during every consecutive session in order to increase the patient’s coping skills. Following the first assessment, various suicidal “drivers” are identified and treated during the CAMS course. Ongoing CAMS care consists of developing adequate coping skills (through the stabilization plan) and helping the patient identify and cope with their drivers of suicidality in a problem-oriented way. In CAMS, suicidal drivers are divided into two categories: direct and indirect drivers. Direct drivers are thoughts, feelings, or behaviors that increase specific suicidal thoughts or feelings. Indirect drivers are factors that themselves do not produce suicidal states but instead increase the vulnerability to such states (e.g., unemployment, economic difficulties, trauma from the past).

There are no mandatory homework assignments during a CAMS course. The duration of CAMS care is dependent on the treatment progress and varies between patients. Treatment is concluded when adaptive coping skills are developed while the patient scores him/herself below 3 on subjective suicidal risk on the SSF during three consecutive CAMS sessions. Clinicians in the inpatient acute ward have reported that this criterion implies extended inpatient stays in the clinic, which is deemed unacceptable. Therefore, a deviation from the manual is necessary. However, when recruiting from the inpatient acute wards, we will aim to include those who are believed to stay for longer than only a couple of days and only those who are believed to be able to have at least three sessions with their allocated clinician after randomization. We will analyze all patients who have received three or more CAMS sessions.

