### Procedures to prevent treatment leakage or contamination

The project collaborates closely with the clinical units and teams participating in the trial. Leaders and clinicians are informed about the study design, purpose, and procedures as well as the importance of not contaminating the study by offering TAU participants CAMS treatment. CAMS training and supervision is offered to eligible therapists for the project only. Those who did participate at the training courses are instructed not to deliver CAMS treatment components to any patient who might be a potential participant to the trial in the future. Clinicians who have attended CAMS training and who for some reason are not participating in the project as CAMS therapists are not accepted in the TAU arm.

Furthermore, we ensure that all clinicians are informed about the trial through a system for “critical information” in the electronic patient journal system that is common to all clinical units. Each time a project participant’s journal is opened, a dialogue box appears and informs about his/her attendance in the trial and that CAMS treatment components are not to be added — especially not the SSF. Of note, three inpatient units have used the SSF as a screening tool for assessing suicidality. Two of these units are not attending the project, and the third unit has discontinued this practice before being accepted as a participating unit in the trial. Consequently, some former patients who seek treatment after a relapse may previously have been screened with the SSF. These patients are excluded and not accepted as trial participants. This is routinely controlled by the first author and one of the research assistants. Lastly, CAMS therapists may not consult patients in the TAU condition.

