### Statistical analysis

We will use generalized linear regression to examine the effects of treatment condition (CAMS versus TAU) upon suicidal thoughts (SSI-C scores) and mental health functioning (OQ-45 scores). Possible moderator effects will be estimated by using an array of covariates, including baseline measures (age, gender, ethnicity, diagnoses, and psychological measures), working alliance, medication during the treatment period, varying treatment length, new treatments delivered during follow-up, and an eventual leakage of CAMS elements into TAU.

Statistical analysis will be by intention to treat. To manage and replace missing data, we will create several sets of plausible imputed data, based on the Bayesian approach, by using multiple imputation procedures for the variables of interest, following the guidelines of Sterne and colleagues [43]. In a further sensitivity analysis we will perform the analysis using the per protocol method, excluding patients who did not complete treatment or missed measurements.

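### The three-session CAMS analysis rule conflicts with intention to treat, has no TAU counterpart, and could bias the comparison in either direction

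*Protocol article*

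**What the plan says.** The Statistical analysis section of the protocol article sets the principle: "Statistical analysis will be by intention to treat". Missing data are to be handled "by using multiple imputation procedures for the variables of interest". It then adds one alternative set: "In a further sensitivity analysis we will perform the analysis using the per protocol method, excluding patients who did not complete treatment or missed measurements". That section does not mention a number of sessions.

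The CAMS intervention section, after describing when CAMS ends and why the acute inpatient ward departs from that, says that recruitment from acute wards will aim to take "only those who are believed to be able to have at least three sessions with their allocated clinician after randomization". The next sentence reads: "We will analyze all patients who have received three or more CAMS sessions". It is not tied to a primary, per-protocol or descriptive analysis, and no rule for TAU goes with it.

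The section on preventing treatment leakage adds: "Lastly, CAMS therapists may not consult patients in the TAU condition". A TAU patient therefore cannot accumulate CAMS sessions under the plan.

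**The concern.** The article contains two statements about who is analysed, and they cannot both define the same comparison. Under intention to treat, a patient allocated to CAMS who attends once and leaves is analysed in the CAMS arm. Under the three-session sentence, that patient is not in the set described.

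This is not a detail left for an analysis plan to supply. Both rules are already stated and they disagree.

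The session rule depends on what happens after allocation, and only CAMS patients can meet or fail it. If it governed the comparison, the CAMS arm would be reduced to those who stayed for three sessions, while TAU patients who left just as early would remain. The arms would no longer be comparable by design. In addition, while the role of the sentence is open, the analysis population could be chosen after the results are known.

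**Working it through.** **1. Is there a reading under which the statements agree?**

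- Taken literally as the trial population, the session rule removes every TAU patient, so it cannot be a two-arm set as written.
- The workable reading for a comparison is a restriction on the CAMS arm only. That contradicts intention to treat.
- It is not the stated per-protocol set either. That set is defined by "excluding patients who did not complete treatment or missed measurements", not by three sessions.
- The recruitment aim for acute wards operates before allocation and so affects both arms alike. It is not a source of this problem, and it does not cure it, because an expectation of three sessions is not the same as receiving them.

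**2. The plan's own figures.** From the Power calculation section: one-sided alpha 0.05, SD 7, difference 4 points, 80 analysed (taken as 40 per arm), 20% drop-out.

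- SE = 7 × √(1/40 + 1/40) = 1.565
- Power = Φ(4/1.565 − 1.645) = Φ(0.911) = 0.819, against the stated 82%
- 80 / 0.80 = 100, as stated

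The sample-size figures reproduce and are not in dispute.

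**3. Effect of a CAMS-only filter.** Let f be the fraction of the CAMS arm excluded, and D the number of BSSI-C points by which the excluded patients' mean lies above (worse than) that of the patients kept. Neither is in the document; both are assumptions.

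- Shift toward CAMS = f × D
- SE = 7 × √(1/40 + 1/(40(1 − f)))
- One-sided type I error = 1 − Φ(1.645 − fD/SE)

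For f = 20%, 32 CAMS and 40 TAU patients remain, so SE = 7 × √(1/32 + 1/40) = 1.660.

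| f | D | Shift toward CAMS (points) | One-sided type I error |
|---|---|---|---|
| 20% | +4 | 0.8 | 0.122 |
| 20% | +5 | 1.0 | 1 − Φ(1.645 − 0.602) = 0.149 |
| 20% | 0 | 0 | 0.050 |
| 20% | −4 | −0.8 | 0.017 |

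Over f = 10-30% and D = −4 to +7, the shift runs from 1.2 points against CAMS (f = 30%, D = −4; error 0.010) to 2.1 points toward CAMS (f = 30%, D = +7; error 0.335).

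**4. Loss of precision.** Even with D = 0, power at a 4-point difference falls from 0.819 to 0.800, 0.778 and 0.750 for f = 10%, 20% and 30%.

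**The case against.** The best defence is that the section governing the analysis is clear: intention to treat, multiple imputation, and per protocol only as a sensitivity analysis. The three-session sentence sits in the intervention description, directly after the explanation of the acute-ward departure. It may be meant only as a minimum dose for counting an acute-ward patient as treated. It also does not contain the word *only*. This is a fair reading, and it limits the point: the main comparison is affected only if the sentence overrides the Statistical analysis section. But the sentence does not say so, and the section it would have to fit with never refers to it.

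Three stronger readings are tempting and are not supported.

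- *The comparison is biased toward CAMS.* The Recruitment part of the Discussion describes brief inpatient stays, and clinicians reporting that suicidality no longer seemed a relevant focus once patients left acute care. Some patients with few sessions may therefore be early improvers, and removing them would work against CAMS.
- *The per-protocol set compares selected CAMS patients with unselected TAU patients.* The exclusion there is written without reference to arm, so TAU patients are filtered too.
- *Completing CAMS means that suicidal risk has resolved, so non-completers are non-responders.* The text says "Treatment is concluded when adaptive coping skills are developed while the patient scores him/herself below 3 on subjective suicidal risk on the SSF", but this describes when treatment ends. It is not offered as the per-protocol definition, and the article says that the acute ward must depart from it. Early discharge, or the therapist ending treatment, are other routes to non-completion. No size of completer bias can be derived from this.

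The inputs f and D are also assumed. The acute-ward recruitment aim should lower f there. The 40 per arm is already net of drop-out, so some early leavers may be counted twice. The shift f × D does not depend on arm size, but the error rates do, and they should be read as illustrative.

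**Conclusion.** The conflict is real and unresolved: a rule based on CAMS attendance after randomisation stands beside a commitment to intention to treat. Any comparison built on that rule loses the protection of randomisation.

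The possible distortion is not trivial against the 4-point target. At 20% excluded, it is 0.8 to 1.0 point toward CAMS with a one-sided error of about 12-15% if the excluded patients are 4 to 5 points worse than those kept. It is 0.8 points against CAMS with an error of about 2% if they are 4 points better. If they do not differ, there is no shift and only some power is lost. These results assume SD 7, 40 per arm before exclusion, no true effect for the error rates, and exclusion in the CAMS arm alone.

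A reader might infer that the primary result will favour CAMS falsely, or that the primary analysis is not intention to treat. The document establishes neither. What it establishes is that the analysis population is stated in two incompatible ways.

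**What to change.** - In the Statistical analysis section, state that the primary analysis includes every randomised patient in the allocated arm, whatever the number of sessions received.
- In the CAMS intervention section, delete the three-session sentence, or label it a supportive, non-randomised analysis that does not replace the primary one.
- Label the per-protocol analysis supportive only, and give it a completion criterion that applies equally to CAMS and TAU.

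A complier-average estimate, or a sensitivity analysis of the imputation assumption, could be added, but the point does not depend on either.

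The cost is a few lines of wording. The downside is that the intention-to-treat estimate may be smaller than one restricted to patients who attended.

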### Power calculation

In calculating power, we use one-sided confidence intervals because previous studies have indicated CAMS to be superior to TAU [18, 23–25]. We use the following assumptions: (1) the main outcome variable BSSI-C score after treatment — which is scored on a 0–38 point scale — has a standard deviation of 7 points [27]; (2) there are equal sample sizes in the experimental and control groups; (3) a four-point difference in BSSI-C scores at follow-up will represent a meaningful clinical difference between CAMS and TAU; and (4) the alpha level is 0.05. Based on these assumptions, 82 % power will be achieved by including 80 participants in the trial, who will be randomized to CAMS or TAU. Assuming a 20 % drop-out rate, our desired sample size is 100 participants at inclusion.

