#### Removal from the trial, safety monitoring, and acceptability

All participating therapists and research assistants are health care professionals with considerable experience in the treatment and care of psychiatric patients with suicidality. With the consent of the patient, a brief report about symptom severity and diagnostic considerations obtained from the research interviews at T1 and T2 will be documented in the hospital electronic patient journal. To avoid confusion of roles and responsibility, all clinicians are reminded about their obligation to independently assess suicide risk and diagnostic assessments.

Non-responders or patients with high symptom severity (CAMS and TAU) who have been discharged from treatment at follow-up will be encouraged to contact their general practitioner for assessment and possible re-referral to treatment. Furthermore, patients with active suicidal ideation will be cared for by hospital staff or transported to an emergency room if necessary. The CAMS (or TAU) therapist is independently responsible for safety issues and will terminate CAMS (or ongoing TAU) treatment if he or she assesses the process to be insufficient or harmful. In such cases the therapist reports this information back to the research assistants. Non-responders in the TAU group are not offered subsequent CAMS treatment.

CAMS previously has been shown to be an effective treatment model [16, 17, 22]. In a pilot study from 2012, Ellis and colleagues found that CAMS was successfully implemented and accepted by both patients and clinicians within the frameworks of inpatient settings [24]. Also, in a Danish outpatient naturalistic study, CAMS was found to be feasible to implement as well as effective for reducing suicidal ideation in ordinary clinical care [25]. Patients reported that the therapeutic CAMS sessions were the essential factor for their improvement. In an online survey where adherence to CAMS treatment components was evaluated, Crowley and colleagues reported that CAMS treatment philosophy and strategies were successfully adopted, considered comfortable, and used with confidence by a large majority of 120 clinicians [42]. On this basis we expect that CAMS will probably be acceptable to the patients and clinicians within our clinic.

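### An unlabelled analysis set of patients with three or more CAMS sessions conflicts with intention to treat and filters one arm after randomisation

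*Protocol article*

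**What the plan says.** Two sections of the protocol article say who is analysed.

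- **CAMS intervention.** Course length is not fixed: "The duration of CAMS care is dependent on the treatment progress and varies between patients". The section then explains that the manual's rule for ending treatment is unworkable on the acute inpatient ward. Recruitment there will therefore aim for patients with longer expected stays, and "only those who are believed to be able to have at least three sessions with their allocated clinician after randomization". The next sentence is: "We will analyze all patients who have received three or more CAMS sessions".
- **Statistical analysis.** "Statistical analysis will be by intention to treat". Missing data are handled "by using multiple imputation procedures for the variables of interest". In a sensitivity analysis, "we will perform the analysis using the per protocol method, excluding patients who did not complete treatment or missed measurements".

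Neither section refers to the other. The article gives no minimum number of TAU sessions for inclusion in any analysis.

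**The concern.** A reader who asks which patients enter the CAMS versus TAU comparison gets two answers. Under intention to treat it is everyone randomised. Under the sentence in the CAMS intervention section it is those who reached a session count, which is known only after randomisation and is counted in CAMS sessions. TAU patients are not meant to receive CAMS, so the count cannot be applied to them. Taken literally, the set contains no TAU patients at all, and the comparator has to be guessed.

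If the obvious guess is made, CAMS patients with at least three sessions are set against all TAU patients. The two groups then no longer differ only by allocation. Patients may fall short of three sessions because they disengaged, because the stay was short, or because the therapist stopped treatment. The safety section says the therapist "will terminate CAMS (or ongoing TAU) treatment if he or she assesses the process to be insufficient or harmful", and that applies to both arms. Only in the CAMS arm would such a stop before session three place the patient outside the stated set.

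Leaving two populations on record for the main comparison also leaves room to choose between them once results are known.

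**Working it through.** **1. Does the three-session set match a population under Statistical analysis?**

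| Set | Defined by | Arms | Label |
|---|---|---|---|
| Intention to treat | Randomisation | Both | Main analysis |
| Per protocol | Treatment completed, no missed measurements | Both | Sensitivity |
| Three or more CAMS sessions | Sessions received after randomisation | CAMS only | None |

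It matches neither. The sentence before it, on patients expected to manage three sessions, concerns recruitment, precedes randomisation and can apply to either arm. It does not supply a TAU minimum for analysis.

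**2. Reproduce the plan's own figure.** Inputs from the Power calculation section: SD 7, difference 4 points on the BSSI-C, alpha 0.05, 80 participants (40 per arm), and for sidedness, "we use one-sided confidence intervals".

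- SE = 7 × √(1/40 + 1/40) = 1.565
- Power = Φ(4/1.565 − 1.645) = 81.9%, against 82% stated (81.3% with the t distribution)
- Enrolment: 80/(1 − 0.20) = 100, as stated

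These figures are not in dispute.

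**3. Bias from filtering one arm.** Let q be the share of CAMS patients with fewer than three sessions, and d their mean BSSI-C score minus that of the CAMS patients kept. The article gives neither, so both are assumptions.

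- Mean of all CAMS patients = mean of those kept + q × d
- With no true effect, the TAU mean equals the mean of all CAMS patients. The filtered comparison is therefore off by q × d points, toward CAMS when d is positive because lower scores are better.
- SE = 7 × √(1/(40(1 − q)) + 1/40)
- One-sided error = 1 − Φ(1.645 − q × d/SE)

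For q = 20%: 40 × 0.8 = 32 CAMS patients remain, and SE = 7 × √(1/32 + 1/40) = 1.660.

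- d = +4: bias 0.8 toward CAMS, which is 20% of the 4-point target; error = 1 − Φ(1.645 − 0.482) = 12.2%
- d = 0: no bias; error 5%
- d = −4: bias 0.8 against CAMS; error 1.7%

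Over a wider range (bias in points toward CAMS, one-sided error in brackets):

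| q | d = −4 | d = 0 | d = +2 | d = +4 |
|---|---|---|---|---|
| 10% | −0.4 (2.9%) | 0 (5%) | 0.2 (6.4%) | 0.4 (8.1%) |
| 20% | −0.8 (1.7%) | 0 (5%) | 0.4 (8.0%) | 0.8 (12.2%) |
| 30% | −1.2 (1.0%) | 0 (5%) | 0.6 (9.7%) | 1.2 (17.1%) |

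**4. Power.** Removing q from the 40 CAMS patients, with no bias, gives 80%, 78% and 75% for q = 10%, 20% and 30%. But those 40 are already net of the 20% drop-out: 50 × 0.8 = 40. If the patients with fewer than three sessions are the same people as the drop-outs, q up to 20% costs nothing further and power stays at 82%. The three lower figures describe the case of no overlap.

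**The case against.** The strongest defence is that the sentence does not say what it might be taken to say. It contains neither a word meaning only nor a word meaning primary, and it excludes nobody explicitly. It closes a paragraph about acute wards where the manual's end-of-treatment rule cannot be met. A natural reading is inclusive: a patient discharged before meeting that rule still counts as treated after three sessions. The per-protocol analysis leaves completion undefined, and this sentence could supply the definition. The section devoted to statistics plainly states intention to treat. The recruitment aim also limits how many acute-ward patients should fall short of three sessions.

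Much of this stands. A reader might infer that the plan has replaced intention to treat with a three-session set as its primary population; the text does not establish that. A secondary or treatment-completion reading is possible. But no such label is given, the Statistical analysis section does not point to this rule, and no TAU counterpart exists under any reading. Every reading needs a change to the text.

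A reader might also infer that the rule necessarily favours CAMS. The document does not support that either. The sentence follows directly on text about short stays, so some patients with fewer than three sessions may have gone home early, no worse or even better than those who stayed.

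**Conclusion.** The concern holds as an unlabelled and conflicting analysis population. The three-session set is defined after randomisation, applies to CAMS only, and matches neither population under Statistical analysis. If it is used for the treatment comparison, the protection of randomisation is lost, whichever way the bias runs.

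The size is unknown, because the article gives neither the share of patients with fewer than three sessions nor how they fare. With an assumed 20% removed, the bias runs from 0.8 points toward CAMS (about 12% one-sided error) if they score 4 points worse, through none, to 0.8 points against CAMS if they score 4 points better. This rests on the plan's SD of 7 in both groups and on 40 evaluable patients per arm before the filter.

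A definite loss of power should not be claimed: it depends on overlap with the 20% drop-out already allowed for. The stated 82% power and the target of 100 are sound on their own assumptions.

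**What to change.** In the Statistical analysis section, state that the primary analysis includes all randomised patients in the arm to which they were allocated, whatever number of sessions they received.

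Then do one of two things with the sentence in the CAMS intervention section:

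- delete it; or
- label the three-session set as secondary, give a comparable minimum for TAU, and say how it relates to the per-protocol definition, including whether three sessions is what counts as completing treatment. Even with a matched minimum, this remains a non-randomised comparison and should be reported as supportive only.

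A complier-average causal effect analysis, with randomisation as the instrument and three sessions as treatment receipt, is optional. It would have to note that the first CAMS session already includes the core assessment, the treatment plan and the stabilisation plan. Patients with one or two sessions have therefore received CAMS content, which strains the exclusion assumption. Session counts should be obtainable from the Suicide Status Form, which is filled out at every CAMS session.

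The cost is a few sentences of wording, with no new data and no change in sample size. The downside is that the reported effect may be slightly less favourable to CAMS.
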